### Specific criteria for withdrawal

Not applicable.

## Replacement of individual subjects after withdrawal

In case of withdrawal, the subject will not be replaced. Power calculations are based on a drop-out rate of 20%.

## Follow-up of subjects withdrawn from treatment

Not applicable

## Premature termination of the study

Premature termination of the study does not need any form of explanation by the subject. Severe physical discomfort, noticed by the principal investigator, coordinatinginvestigator or subjects themselves will lead to immediate termination of the study.

# SAFETY REPORTING

## Section 10 WMO event

In accordance to section 10, subsection 1, of the WMO, the investigator will inform the subjects and the reviewing accredited METC if anything occurs, on the basis of which it appears that the disadvantages of participation may be significantly greater than was foreseen in the research proposal. The study will be suspended pending further review by the accredited METC, except insofar as suspension would jeopardise the subjects’ health. The investigator will take care that all subjects are kept informed.

## Adverse and serious adverse events

Adverse events are defined as any undesirable experience occurring to a subject during a clinical trial, whether or not considered related to the investigational drug. All adverse events reported spontaneously by the subject or observed by the investiga­tor or his staff will be recorded.

A serious adverse event is any untoward medical occurrence or effect that at any dose results in death;

- is life threatening (at the time of the event);
- requires hospitalisation or prolongation of existing inpatients’ hospitalisation;
- results in persistent or significant disability or incapacity;
- is a congenital anomaly or birth defect;
- is a new event of the trial likely to affect the safety of the subjects, such as an unexpected outcome of an adverse reaction, lack of efficacy of an IMP used for the treatment of a life threatening disease, major safety finding from a newly completed animal study, etc.

All SAEs will be reported to the accredited METC that approved the protocol, according to the requirements of that METC.

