# STUDY DESIGN

### Protocol

An outline of the study and the exercise protocol is provided in Figure 1. Subjects will be randomized to a 4-wk supplementation protocol (astaxanthine or placebo) and an exercise performance test will be done before and after the 4-wk intervention. For the exercise performance test, subjects will report to the laboratory at 8.00 h. Resting metabolic rate will be measured by ventilated hood connected to the OmniCal IV for indirect calorimetry and substrate use measurement. Before testing, participants will be weighed, fitted with a heart-rate monitor, and familiarized with the Borg scale of perceived exertion [11]. A Teflon catheter will be inserted in an antecubital vein.

The exercise protocol consists of 60 minutes steady state exercise at 50% Wmax (as determined in trial 1, see paragraph 6.3: pretesting). Subsequently, a time-trial of about an hour will be conducted. This type of time-trial has been validated and used before in our lab[12], see for an overview of validation studies Currell and Jeukendrup [13]. Examples of coefficients of variation in similar trials are 1.1 [14], 0.7 [15] and 0.9 [16].

Subjects will be instructed to perform a set amount of work in the shortest time possible. Total work to be performed will be calculated according to the equation of Jeukendrup, Saris, Brouns, and Kester [17], adapted based on previous experiences [12] :

Total amount of work = 0.60 · Wmax · 3,600

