# TREATMENT OF SUBJECTS

## Investigational product/treatment

### Supplements

Subjects will be provided with either astaxanthin or placebo supplements. Subjects have to ingest 2 capsules of 4 mg with breakfast and 3 capsules with dinner throughout the 4 wk intervention period, to ascertain an intake of 20 mg/day. Astaxanthin has been shown to be safe in both animals [18] and humans [19, 20], and has recently received GRAS (generally recognized as safe) status by the US Food and Drug Administration [21]. This document also gives an excellent overview of all toxicological studies that have been performed (see attached file). Astaxanthin is produced by BioReal (Sweden). A certificate of safety for human consumption is attached.

The astaxanthin pills contain an algae extract high in astaxanthin, dissolved in sunflower oil in gelatine capsules (see attached file). The placebo treatment will consist of sunflower oil in gelatine capsules, without the astaxanthin. Treatments will look and taste identical. An independent person will randomly assign the subjects to a treatment so that both the subjects and the investigators involved in the study will be blinded to the treatment.

Astaxanthin or placebo pills have to be taken with meals (breakfast and dinner) twice daily. Astaxanthin and placebo pills will be send directly to the investigator. The supplements will be stored in a locked cabinet at room temperature, until the pills will be provided to the subjects. Compliance will be determined by the amount of pills that are left after the 4 week supplementation protocol.

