## Follow-up of adverse events

All adverse events will be followed until they have abated, or until a stable situation has been reached. Depending on the event, follow up may require additional tests or medical procedures as indicated, and/or referral to the general physician or a medical specialist.

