## Benefits and risks assessment, group relatedness

There are no benefits for the subjects in participating in the study, except for a possible performance enhancing effect of the astaxanthin supplementation. The risks involved in participating in this experiment are minimal. Astaxanthin has been shown to be safe. Insertion of the catheters in a vein is comparable to a normal blood draw and the only risk is of a small local haematoma.

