## End of study report

The sponsor will notify the accredited METC and the competent authority of the end of the study within a period of 90 days. The end of the study is defined as the last patient’s last visit.

In case the study is ended prematurely, the sponsor will notify the accredited METC and the competent authority within 15 days, including the reasons for the premature termination.

Within one year after the end of the study, the investigator/sponsor will submit a final study report with the results of the study, including any publications/abstracts of the study, to the accredited METC and the Competent Authority.

Estimated time scheduled:

Start: November 1st 2010 (start immediately following approval MEC)

End: March 1st 2011

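### Section 7.2 relies on volunteered or observed adverse events, with no enquiry described over the 4 weeks of home dosing and no contact after trial 4, so minor events may be under-recorded

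*Protocol*

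**What the plan says.** - **Routes of capture (7.2).** The sentence that sets the method is "All adverse events reported spontaneously by the subject or observed by the" investigator or staff. No questionnaire, checklist, diary or standard question is described anywhere in the protocol.
- **Which events count (7.2).** "Adverse events are defined as any undesirable experience occurring to a subject during a clinical trial". No start or stop date for collection is given.
- **Follow-up (7.3).** "All adverse events will be followed until they have abated, or until a stable situation has been reached".
- **Exposure (3.1.1 and 5.1.1).** Capsules are taken at breakfast and dinner for 4 weeks, and "an exercise performance test will be done before and after the 4-wk intervention". The one check stated for the end of that period concerns intake: "Compliance will be determined by the amount of pills that are left after the 4 week supplementation protocol".
- **Named risk (9.4).** Of catheter insertion the protocol says that "the only risk is of a small local haematoma". Blood is sampled in trials 2, 3 and 4 (6.3.4).
- **End of study (10.4).** "The end of the study is defined as the last patient’s last visit".
- **Withdrawn riders (6.6).** Follow-up is marked as not applicable.

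**The concern.** How adverse events are found is a matter for the protocol, and this protocol does fix it: an event is recorded if the rider brings it up or if staff happen to see it. During the only period of exposure staff are not described as seeing the rider, so the second route is closed and everything depends on the first. Whether a mild complaint in week 2 is recorded then depends on whether the rider thinks it worth mentioning, not on a question that everyone in both arms was asked.

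The second gap is at the end. Trial 4 is the last described visit and includes a venous catheter, six blood samples and a time trial. A bruise that shows only after the rider has gone home would reach the record only if he contacts the team.

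At stake is the quality of the safety description. The protocol calls the risks minimal (summary and 9.4) and obliges the investigator to act if the disadvantages prove greater than foreseen (7.1). That obligation can be met only as well as events are noticed.

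**Working it through.** The point rests mainly on reading sections together, and the arithmetic only gives scale.

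**1. The plan's own figure.** The only design figure is the sample size (4.4): SD 1.3%, difference 1.7%, z values 1.96 and 0.84. Per group, n = 2 × (1.3 × (1.96 + 0.84) / 1.7)² = 9.17, and 9.17 / 0.8 = 11.46, rounded up to 12. This reproduces the stated 12 per group and 24 in total. The present point does not depend on it except for the counts below.

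**2. Home period.** Section 3.1.1 places one test before and one after supplementation, and 5.1.1 places intake at home meals in between. The text describes no contact in that interval. Figure 1 could not be read in the copy examined, so this statement rests on the text. Planned intake time is 24 riders × 28 days = 672 rider-days, of which 12 × 28 = 336 are on astaxanthin. This is exposure time without a described enquiry. It is not a count of missed events.

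**3. Catheter sessions.** Trials 2, 3 and 4 are the same test (6.3.1), so 24 × 3 = 72 sessions are planned. After trials 2 and 3 (48 sessions) the rider returns and a catheter is again placed in an antecubital vein, so staff may see a remaining bruise. After trial 4 (24 of 72) no later visit is described.

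**4. Collection window.** Section 7.2 refers to events during the trial. Section 10.4 sets one study-level date for notification. Section 7.3 follows recorded events until they resolve or stabilise. None of the three says when collection starts or stops for an individual rider. Section 7.3 applies once an event is known, so it does not help an event that nobody reports.

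**5. Illustration of what incomplete capture does.** Let p be the true risk of an event and c the share of events recorded. Both are assumed, since the protocol gives neither. With n = 12 on astaxanthin, the chance of recording at least one event is 1 − (1 − p·c)^12.

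| p | c = 1 | c = 0.5 | c = 0.25 |
|---|---|---|---|
| 0.10 | 0.72 | 0.46 | 0.26 |
| 0.20 | 0.93 | 0.72 | 0.46 |

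For p = 0.10 and c = 0.5, for example, 1 − 0.95^12 = 0.46. Halving capture costs as much as halving the true risk, and a group of 12 has little information to spare.

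**The case against.** The strongest reply is that safety is neither an objective nor an endpoint (sections 2 and 6.1), that the subjects are healthy young men, and that the statements on safety rest on cited earlier work (5.1.1), not on this trial. Riders and investigators are blinded (6.2), so readiness to report should not differ systematically between arms. A catheter haematoma is a procedural event common to both arms and says nothing about astaxanthin. Serious events and unforeseen disadvantages must still be reported to the ethics committee (7.1, 7.2). All of this stands, and it limits the weight of the point. It does not show that the stated method is a good one.

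Several stronger readings are tempting but not supported:

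- **Collection stops at each rider's last visit.** A reader might infer this from 10.4, but that section defines a single study-level date for notification. Every rider who finishes before the last one can still report within the study, and 7.3 does not fit a hard stop. The protocol defines no window, which is a different matter.
- **Events go largely uncaptured.** That needs a capture rate, and the protocol gives none. Spontaneous reports can be made on any of the 672 rider-days.
- **Haematomas after trials 2 and 3 are recorded only if volunteered.** Staff may see them at the next test. A bruise from trial 3 may have faded after 4 weeks, but the interval from trial 2 to trial 3 is not stated.
- **Zero events in 12 riders would still allow a true rate of 22%.** The one-sided 95% limit, 1 − 0.05^(1/12) = 22.1%, is correct, but it follows from the group size and would be the same with perfect questioning. It is not evidence about the collection method.

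**Conclusion.** The point holds as a minor one. Ascertainment is passive, no enquiry is described for the period that contains all the exposure, no contact is described after trial 4, and no collection window is stated. Minor supplement effects, and late catheter-site haematomas after trial 4, may be under-recorded.

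The size can be given only as scope: 672 planned rider-days and 24 of 72 planned catheter sessions, both at full retention. The number of events lost is unknown. The conclusion assumes that Figure 1 adds no contact beyond those in the text. No primary or secondary result changes.

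**What to change.** In 7.2, keep spontaneous and observed reporting and add to it; replacing it would remove the only stated route for reports from home.

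- Put the same open, non-leading question about any complaint since the last visit to every rider, by blinded staff, at trials 3 and 4. At trial 4 it can accompany the capsule count.
- Optionally, make one brief telephone or e-mail contact a few days after trial 4. Without it, a late bruise after trial 4 still depends on the rider volunteering it.
- State the collection window as running from the first test procedure to that last enquiry.

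The end-of-study definition in 10.4 need not change.

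The cost is one line on the visit forms, a few more minor complaints recorded in both arms and, if the contact is used, 24 short calls or messages. One limit remains: the trial 4 question does not reach riders who withdraw before trial 4. At the assumed 20% drop-out that could be up to about 5 of 24 (0.20 × 24 = 4.8).

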### Suspected unexpected serious adverse reactions (SUSAR)

Based on previous comparable studies no SUSARs are expected (see safety issue addresses under “5.1.1 supplements”

### Annual safety report

Not applicable.

## Follow-up of adverse events

All adverse events will be followed until they have abated, or until a stable situation has been reached. Depending on the event, follow up may require additional tests or medical procedures as indicated, and/or referral to the general physician or a medical specialist.

## Data Safety Monitoring Board (DSMB)

Not applicable.

# STATISTICAL ANALYSIS

## Descriptive statistics

All data will be presented as means ± SEM. Statistical analysis of the data of performance will be performed using a repeated measures anova with time (pre-post) and treatment (astaxanthin vs placebo) as factors. Likewise, differences between treatments in plasma insulin, plasma glucose, plasma FFA, plasma astaxanthine, and whole-body fat oxidation following the intervention will be analysed with 2-way repeated measures ANOVA, with time as within-subjects factor, and treatment as between-subjects factor. Statistical significance will be set at P<0.05. Data will be analyzed with SPSS 15.0 (SPSS inc, USA).

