where Wmax is the maximal workload capacity determined at Visit 1 and 3,600 is the duration in seconds (equivalent to 1 hr). The ergometer will be set in linear mode so that 60% Wmax will be obtained when the participants cycle at their preferred cadence, which had been determined during Visit 1. The ergometer will be connected to a computer that calculates and displays the total amount of work performed. The only information participants receive is the absolute amount of work performed and the percentage of work performed relative to the set amount of work. This information will be displayed on a computer screen in front of the ergometer. A fan will be placed 1 m behind each participant to provide cooling and air circulation during the trials. The rating of perceived exertion (RPE) will be recorded at the start and when the time trial is completed, and heart rate (Polar, Finland) will be recorded continuously throughout the test. During none of the time trials, interaction will occur between the participant and the investigators except for Borg-scale recording. No encouragement will be given to the participants, and they will be kept unaware of performance-related information such as exercise time, heart rate, and cycling cadence.

Breath gas analysis will be performed during the steady state exercise for 5 minutes before every blood draw (15, 30, 45, 60 min) by indirect calorimetry with an OmniCal IV. Water will be provided during exercise ad libitum. 8 Blood samples (8ml) will subsequently be taken from an antecubital vein at t=0, 15, 30, 45, 60 and directly after completion of the time-trial.

***
[figure not shown]
***

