## Study procedures

### Pretesting

Body weight will be measured with a digital balance with an accuracy of 0.001 kg (E1200, August Sauter GmbH, Albstadt, Germany).

All subjects will participate in a cycling test (trial 1) to determine maximal oxygen uptake (VO2 max) and maximal workload capacity (Wmax). After a 5 min warm-up at 100 W, workload will be set at 150 W and will be increased with 50 W every 2.5 min until exhaustion [22]. O2 uptake and CO2 excretion, workload (W), cadence (rpm) and heart rate (Polar, Finland) will be recorded at every interval. The appropriate seat position, handle bar height and orientation will be determined and replicated in each subsequent visit. A familiarization trial (trial 2) will be performed to reduce learning effect over the pre and post exercise tests. The familiarization trial is identical to trials 3 and 4 (see paragraph 3.1: “protocol”)

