### Analysis

A total of 6 blood samples (8 ml) in trial 2, 3 and 4 will be collected in EDTA containing tubes and centrifuged at 1000 g and 4°C for 10 min. Aliquots of plasma will be frozen in liquid nitrogen and stored at –80°C until analysis. Glucose (Uni Kit III, Roche, Basel, Switzerland) and insulin will be analysed by radio immunoassay (Linco, Human Insulin RIA kit). Plasma free fatty acid concentrations will be analyzed with the NEFA C test kit from Wako Chemicals (Neuss, Germany). Astaxanthin content in plasma will be analyzed by reverse phase HPLC (Alliance 2690, Waters, Milford, MA). Breath gas analysis will be performed with an Omnical gas analyzer. Cardiac Troponin T will be measured by using the high-sensitivity cTnT assay on the Elecsys 2010 (Roche Diagnostics).

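### The two-way ANOVA for fat oxidation and plasma outcomes has one undefined time factor, but the schedule has two within-subject dimensions

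*Protocol*

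**What the plan says.** Section 8.1 (Descriptive statistics) first gives the model for time-trial performance: a "repeated measures anova with time (pre-post) and treatment (astaxanthin vs placebo) as factors". Here time is defined.

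The next sentence begins "Likewise, differences between treatments in plasma insulin, plasma glucose, plasma FFA, plasma astaxanthine" and goes on to fat oxidation: "whole-body fat oxidation following the intervention will be analysed with 2-way repeated measures ANOVA, with time as within-subjects factor", with treatment as the between-subjects factor. Here time is not defined.

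The data to be analysed are described elsewhere in the protocol:

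- **Pre and post.** Section 3.1.1 states that "an exercise performance test will be done before and after the 4-wk intervention". Section 6.3.1 numbers the tests: "The familiarization trial is identical to trials 3 and 4". Trial 2 is therefore familiarization, and trials 3 and 4 are the pre and post tests.
- **Minute within a trial, gas exchange.** Section 3.1.1: "Breath gas analysis will be performed during the steady state exercise for 5 minutes before every blood draw (15, 30, 45, 60 min"). A resting measurement by ventilated hood is made in the same session.
- **Minute within a trial, blood.** Section 6.3.4: "A total of 6 blood samples (8 ml) in trial 2, 3 and 4 will be collected". Section 3.1.1 lists six times: 0, 15, 30, 45 and 60 minutes, and the end of the time trial.

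Section 8.1 names no within-trial summary (such as a mean or area under the curve), no baseline covariate and no second within-subject factor.

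**The concern.** A two-way ANOVA with treatment between subjects has room for one within-subject factor. The schedule produces two. The sentence can be read in two ways, and each leaves a gap.

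- **Time is minute within trial 4.** The words about the period after the intervention point this way. The subject's own trial 3 values are then collected but not used.
- **Time is pre/post.** *Likewise*, placed directly after a sentence that defines time as pre/post, points this way. Trial 3 is then used, but four exercise gas measurements or six blood samples per trial must first be reduced to one value, and the protocol does not say how.

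Fat oxidation is the proposed mechanism in the introduction and the named secondary endpoint in section 2. As the text stands, its test could be a trial 4 treatment effect, a treatment-by-minute interaction, or a pre/post interaction on a summary chosen later. These can give different answers, and with about 10 completers per group they can differ considerably in precision.

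**Working it through.** **The plan's own figure.** Section 4.4 uses SD 1.3%, difference 1.7%, z values 0.84 and 1.96, and 20% drop-out. Then n = 2 × (1.3 × 2.80 / 1.7)² = 9.17 per group, and 9.17 / 0.8 = 11.5, rounded up to the stated 12. The figure reproduces. It concerns time-trial performance, and no sample size or power is stated for fat oxidation or plasma outcomes. I take from it only that about 10 per group complete (12 × 0.8 = 9.6).

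**Values per subject in trials 3 and 4.** Exercise gas measurements: 2 × 4 = 8, or 2 × 5 = 10 with rest. Blood samples: 2 × 6 = 12. These form a grid of pre/post by minute, and one within-subject factor indexes only one side of it.

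**Cost of each reading.** Take a subject's steady-state mean in each trial, with equal variance σ² in trials 3 and 4, correlation ρ between them, and n per group. The variance of the treatment contrast is:

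- trial 4 only: 2σ²/n
- pre/post interaction (difference in change): (2σ²/n) × 2(1 − ρ)
- trial 4 adjusted for trial 3: (2σ²/n) × (1 − ρ²)

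Relative to the adjusted analysis, trial 4 only has 1/(1 − ρ²) times the variance. The interaction has 2(1 − ρ)/(1 − ρ²) = 2/(1 + ρ) times the variance. The protocol gives no ρ, so I show a range.

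| Assumed ρ | Trial 4 only, 1/(1 − ρ²) | Pre/post, 2/(1 + ρ) |
|---|---|---|
| 0.3 | 1.10 | 1.54 |
| 0.5 | 1.33 | 1.33 |
| 0.7 | 1.96 | 1.18 |
| 0.8 | 2.78 | 1.11 |

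The two readings are equally precise at ρ = 0.5. Below that the trial 4 comparison is the better of the two, and above it the interaction is. In standard errors, the trial 4 comparison is wider than the adjusted one by about 5%, 15%, 40% and 67% (square roots of the middle column).

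**What this means for power.** As an illustration, take 10 per group, a two-sided 5% level, a true difference of 1 SD of a trial 4 value, and a noncentral t with 18 degrees of freedom. The 1 SD is my assumption.

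| Assumed ρ | Trial 4 only | Pre/post | Adjusted |
|---|---|---|---|
| 0.3 | 56% | 43% | 60% |
| 0.5 | 56% | 56% | 69% |
| 0.7 | 56% | 78% | 84% |
| 0.8 | 56% | 92% | 94% |

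The adjusted figures ignore the small cost of estimating the covariate slope, so at low ρ the real gain is less than shown.

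**The case against.** The strongest reply is that the sentence should be read with the one before it. Time has just been defined as pre/post, *Likewise* carries that over, and the reference to the period after the intervention merely describes the effect sought. A steady-state mean or area under the curve then fits a two-way model and uses every sample. The choice of summary could sit in a statistical analysis plan. The outcomes are secondary, and the primary analysis is explicitly pre/post.

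Much of this stands. A reader might infer that the trial 3 baseline is certainly discarded; the text does not support that, because the pre/post reading keeps it. Nor does the pre/post reading make the within-trial samples unusable. What remains is that the protocol states a model rather than deferring it, and that this model does not say which of two dimensions its single factor represents.

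Three other inferences are also tempting and should not be drawn:

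- **That subjects with a missing sample will be dropped.** That is how classical repeated-measures ANOVA usually behaves, but the protocol states no missing-data rule and no loss rate, and such a rule may be in the analysis plan.
- **That every analyte is measured serially.** Sampling times are given, but not which samples are assayed for what. For plasma astaxanthin, serial measurement is not established.
- **That a trial 4 comparison would be biased.** Treatment is randomised, so it loses precision and is exposed to chance baseline imbalance, but is not biased by design.

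**Conclusion.** The point holds as a mismatch between model and schedule. For gas exchange and blood draws there are two within-subject dimensions, and section 8.1 provides one factor and leaves it undefined.

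The size depends on the reading and on an unknown correlation. Against an analysis adjusted for trial 3, the variance is 1.10 to 2.78 times as large if only trial 4 is used, and 1.54 down to 1.11 times if the pre/post interaction is used, for ρ from 0.3 to 0.8. These ratios assume equal variances in the two trials and ignore the estimation of the slope. On those terms the adjusted analysis is at least as precise as either reading at every ρ shown, so the recommendation does not depend on which reading was meant.

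The primary endpoint is unaffected. The change is worth making because it improves precision with data already planned and settles the fat-oxidation test in advance.

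**What to change.** In section 8.1, replace the sentence on secondary outcomes with text to this effect, before any outcome data are examined by treatment:

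- **Exercise fat oxidation.** Compare the trial 4 mean over the steady-state windows (15, 30, 45 and 60 minutes) between treatments, with the subject's trial 3 steady-state mean as covariate. Report the adjusted difference with its 95% CI, and name this as the test for exercise fat oxidation.
- **Resting fat oxidation.** Analyse the trial 4 resting value in the same way, with the trial 3 resting value as covariate.
- **Serially sampled plasma outcomes.** Fit trial 4 values with treatment, minute and treatment-by-minute, the subject's trial 3 mean as covariate, and subject as random effect. Using the trial 3 mean rather than the same-minute value avoids losing a trial 4 row because its single matching baseline sample is missing.
- **Assays.** State which analytes are measured at which sampling times, so that it is clear to which outcomes the serial model applies.

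If the investigators prefer to keep an ANOVA, the minimum is to define time and state a treatment by pre/post by minute model.

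The cost is a few sentences in section 8.1 and slightly more programming. No additional visits, samples or subjects are needed.
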